## Abstract

**Background:**

Addiction research has hypothesised that automatic and reflective cognitive processes play an important role in the onset and maintenance of alcohol (ab)use, wherein automatic reactions to drug-related cues steer the drug user towards consuming before reflective processes can get over and steer towards a different behavioural response. These automatic processes include the tendency to attend and approach alcohol cues. These biases may be trained away from alcohol via computerised cognitive bias modification (CBM). The present protocol describes the design of a double-blind randomised controlled trial (RCT) testing the effectiveness of attentional bias and approach bias re-training with a 2×2 factorial design, alongside a brief motivational support (MS) program.

**Methods/Design:**

Participants (n = 120) are adult alcohol dependent outpatients, recruited from a public health service for addiction in Italy, who have been abstinent for at least two months, and with a main diagnosis of alcohol dependence disorder. Participants are randomly assigned to one of four experimental conditions and complete 11 sessions of training after a baseline assessment. The MS takes place before each training session. Post-intervention and three-month follow-up assessments examine the change in clinical outcome variables and attentional and approach biases (measured with the Visual Probe Task and the Approach-Avoidance Task, respectively). Alcohol approach-avoidance implicit memory associations (measured with the Brief Implicit Association Test) are also evaluated at pre- and post-intervention to explore generalisation effects. Primary outcome measure is relapse rate at follow-up. Secondary outcome measures include change in cognitive biases, in alcohol-related implicit memory associations, and in the clinical variables assessed. An exploratory analysis is also planned to detect interaction effects between the CBM modules and possible moderators (interference control capacity, gender, age, number of previous detoxifications) and mediators (change in cognitive bias) of the primary outcome measure.

**Discussion:**

This RCT is the first to test the effectiveness of a combined CBM intervention alongside motivational support in alcohol-dependent outpatients. The results of this study can be extremely valuable for future research in the optimisation of CBM treatment for alcohol addiction.

**Trial registration:**

Current Controlled Trials ISRCTN01005959 (registration date: 24 October 2013).

**Electronic supplementary material:**

The online version of this article (doi:10.1186/s13063-015-0576-6) contains supplementary material, which is available to authorized users.

## Background

People with an addiction disorder often describe their substance (ab)use as a somewhat ‘unconscious’ decision, something that happens ‘by chance’ and without any intentional planning or awareness. However, many drug users are conscious of the detrimental effects of substance abuse and seek treatment to abstain from consuming, citing rational considerations such as the costs of continued substance use outweighing the benefits. Nevertheless, the risk for lapse and relapse remains extremely high. This paradoxical and deleterious pattern of behaviour encouraged research into the mechanisms underlying drug-seeking behaviour even when explicit motivations to quit are present.

It has been long known that behaviour is not only driven by rational and conscious processes, but also driven by mechanisms that go beyond intentionality (see Hofmann *et al*. [1]). Recently, this realisation has gained relevance in addiction research, resulting in efforts examining the role played by relatively automatic processes in the onset and maintenance of addictive behaviours [2-7]. At a descriptive level, dual-process models of addiction point towards two qualitatively different classes of information processing mechanisms underlying behaviour, namely:Automatic processes, which are initial, fast, associative and impulsive processes evoked by drug-related stimuli, that operate at early stages of response selection through associative links and emotional and motivational associations [7]. When an automatic process leads to impulsive responses or task interference conflicting with explicit task goals, as may well be the case in drug addiction, they are frequently referred to as *cognitive biases*. Cognitive biases are based on associative learning processes and prior reinforcement and are by nature difficult to voluntarily change and control. Examples of cognitive biases are selective attention (for example, alcohol dependents’ attention is usually automatically and selectively drawn by alcohol-related cues), substance-related automatic associations in memory (for example, alcohol being repeatedly and automatically associated to positive or negative feelings) and action tendencies towards the substance (for example, an automatic tendency to approach alcohol cues) [8].Reflective processes, which are slower, relatively controlled propositional processes that include ‘rational’ decision-making and emotion regulation. Reflective processes continuously update and integrate initial inputs into more coherent and complex mental representations in order to optimise the selection of the final behavioural outcome [7,9,10]. To achieve this, top-down control is deployed over impulses to integrate them with explicit motives, beliefs and expectancies about the long-term behavioural outcomes and goals [9,10].

The two classes of processes depend on each other and synergistically interact in determining behaviour. That means there is no process that is purely reflective or automatic, though the degree to which each is a more prominent determinant can be distinguished on the basis of their *latency*. For instance, an initial automatic reaction to a positive incentive stimulus can be evoked (bottom-up input), such as an approach response to a glass of wine. After that, the initial reaction can (or cannot) progressively unfold into the action of grabbing the glass and drinking it under the gradual influence of conscious goals and motivation (top-down regulation), such as the explicit goal of alcohol abstinence to re-gain the lost job position [7,9,10].

According to this dual-process perspective, the ‘addiction paradox’ can result from an imbalance between strengthened automatic reactions to substance-related cues that have acquired a high incentive salience after repeated consumption, while weakened reflective processes and cognitive control are obstructed before they can determine the optimal behavioural response [7,8,11]. This imbalance between the operating processes makes the individual more at risk of being triggered by drug cues, thus being automatically prompted to consume the drug, while any deliberate decision to abstain is too late to prevent the individual from consuming [3,7,8].

Since both strengthened automatic reactions to alcohol cues and weakened reflective processes may be interwoven in alcohol-related problems, they both may be targeted in interventions. Reflective processes are usually the focal target of standard treatment interventions, such as cognitive behavioural therapy, counselling and motivational interviewing. A common approach across such interventions consists of the therapist and patient making an explicit analysis of the pros and cons of the patient’s alcohol use, of related motives and expectancies and of strategies and long-term goals to enact deliberate control.

More recently, a new family of interventions, collectively called Cognitive Bias Modification (CBM), has been developed to tackle prepotent, drug-evoked automatic processes involved in addiction [8,12,13]. CBM paradigms are computerised tasks aimed at training alternative responses to a drug-related stimulus in order to adjust the biases that underlie the breakdown in controlled processes. Typically, they are modified versions of assessment tasks, such as the Approach-Avoidance Task (AAT) [14,15], with a built-in contingency that recasts them to re-training paradigm.

The first clinical applications of CBM paradigms as an add-on to standard interventions such as cognitive behavioural therapy have shown promising results [16-19]. Two randomised controlled trials (RCTs) with German alcohol-dependent inpatients did demonstrate that an approach bias for alcohol stimuli could be re-trained, with a generalisation of the training effects beyond the experimental procedure context [18,19]. Moreover, participants in the training condition had a lower rate of relapsing within one year after discharge, after controlling for gender in Wiers *et al*. [18], and for age and number of previous detoxifications in Eberl *et al*. [19]. A study with Dutch alcohol-dependent inpatients showed the success of an attentional bias re-training in increasing the ability to disengage from alcohol stimuli, with a generalisation to untrained, new stimuli and a significantly longer time until relapse for the experimental group in the follow-up period [17].

These results could suggest that computerised CBM has the potential to be an effective intervention that can be easily incorporated into standard health care practices, alongside standard treatments. As a next step, it is important that the findings are replicated and extended across various patient categories and delivery modes, for example by combining different CBM paradigms. To the best of our knowledge, there is only one ongoing RCT testing a completely online CBM intervention combining the CBM training for alcohol approach bias, attentional bias and automatic memory associations among problem drinkers [20]. However, no studies have yet investigated the effectiveness of a combined CBM intervention with alcohol-dependent outpatients. Unlike residential treatment programs, the outpatient treatment regimen does not provide patients with the safe, secure and structured environment that isolates them from negatively influencing factors and tempting conditions. Patients return to their own daily environments after outpatient alcoholism treatment, and must voluntarily abstain from alcohol use, which requires a greater amount of diligence and efforts. Therefore, this group of patients is also likely to receive potential benefits from this type of interventions.

Finally, inspired by the dual-process account of addictive behaviours previously presented, which emphasises the interaction between bottom-up and top-down processes [7-10], this study is the first to include a targeted motivational support (MS) intervention alongside the combined CBM training, in order to integrate long-term goals with the training and tackle deliberate and conscious explicit motivational processes related to the patients’ experience of re-training their alcohol-triggered automatic responses. The main goal of combining CBM with a motivational approach is to enhance motivation to train and harness the individual’s capacity for change [21]. At the start of each training session a brief MS interview is then included on top of the CBM training, with a threefold objective:To stimulate and bolster the explicit motivation and reasons for doing the training (goal maintenance, recall of long-term expected outcomes and top-down influence), which can act as a fuel to develop and exert control to overcome the appetitive motivational and automatic reactions towards alcohol [7,8];To provide continual feedback about the participant’s subjective performance on the training (incentive value);To promote the acceptability of the training ([7,8]) by increasing engagement to intervention (fostering commitment to change).

### The present study: aims and hypotheses

The aim of the current study is to investigate the effectiveness of combining computerised alcohol attentional bias and approach bias CBM trainings in adult alcohol-dependent outpatients alongside a motivational approach to sustain the training progression. The primary goal is testing the main and added effects of the CBM interventions on remission progress from alcohol addiction immediately after the intervention and three months later, with changes in the number of lapse or relapse episodes as primary outcome measure. It is expected that, for each of the two CBM training modules, participants in the active training condition will show a lower percentage of lapse or relapse than participants in the placebo condition [16-19].

Secondary outcome measures include changes in alcohol-related cognitive biases following the combined CBM intervention. Interaction effects between the CBM modules are explored, as well as the additive effect of exposure to the combination of the two CBM trainings. It is expected that each CBM paradigm will decrease or reverse the targeted bias and that these changes might mediate the effects on the clinical outcome (see Eberl *et al*. [19]). Further, it is expected that joint exposure to both active CBM re-trainings will have a greater beneficial effect than each of the active CBM re-trainings separately.

Additionally, we study whether CBM effectiveness is moderated by participant characteristics, namely interference control capacity and strength of the cognitive biases at pre-test. Individual differences in executive functioning can moderate whether the initial automatic reaction towards a glass of wine can be effectively and easily controlled or not. It has been suggested that prolonged alcohol use can negatively affect the deployment of reflective processes (such as interference control and working memory capacity [22,23]), thereby reducing the cognitive capacity available for controlling automatic impulses [8]. Hence, alcohol dependents with a relatively weak ability to inhibit a prepotent approach response (low interference control capacity) may find it more difficult to remain abstinent than those with a relatively strong ability to inhibit a pre-potent response. CBM interventions could be particularly beneficial for those who present relatively poor interference control capacity and/or strong automatic reactions demanding great control efforts. Therefore, in line with dual-process models of addiction and prior findings [8,18,19,24-26], it is expected that participants with strong automatic biases and/or weak interference control will benefit more from the CBM intervention than participants with weaker biases and/or stronger executive functions.

Finally, the effect of several independent clinical variables (such as age, gender and number of previous detoxifications) on the primary and secondary clinical outcomes will be explored, in particular the type of treatments participants are receiving alongside the CBM, such as medication intake and/or other psychotherapeutic interventions.

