## Methods/Design

### Trial design

The present study is a phase II, double-blind, parallel group RCT. Following the design of previous CBM studies [18,19], participants complete 11 sessions of either the active or placebo version of both attentional and approach bias training modules. The experimental intervention has a 2×2 factorial design, which combines the active and placebo training modules into four experimental conditions: one double active training experimental condition, two experimental groups receiving one active training and one placebo training and one double placebo training control group. According to the experimental design, the probability of receiving at least one active CBM intervention reaches 75%. The placebo version of each training module consists of a continuous assessment, in which half of the trials train the cognitive biases away towards alcohol and the other half towards soda (active placebo). The manipulation of the stimulus-response contingency in each task allows for a controlled and clean comparison between experimental conditions while retaining the same tasks, stimuli and instructions. Also, Wiers *et al*. [18] found no differences between continuous assessment and no-training placebo conditions, which suggested that either type of placebo could be used.

Participants complete a total of 14 sessions: two baseline assessment sessions, 11 training sessions, one post-intervention assessment session and one three-month follow-up assessment session. Participants complete the training sessions with a between-session time interval of a maximum of five days. The post-intervention assessment takes place between the 10th and 11th training session during a ‘masked’ session (participants do not know they are completing the post-intervention evaluation). That is to avoid possible negative feelings related to the final ‘evaluation’ of the intervention and minimise self-presentation biases and/or preparatory strategies.

Participant flowchart as per Consolidated Standards of Reporting Trials (CONSORT) statement [27] is presented in Figure 1. The study was approved by the Ethics Committee of the School of Psychology of the University of Padova (March 2013; Protocol number: 1242) and registered at Current Control Trials (identifier: ISRCTN01005959).

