**Table 1 Tab1:** **Measurement instruments: purpose, measures and time points**

**Purpose**	**Measures**	**Baseline**	**Training**	**Post-intervention**	**Follow-up**
Cognitive bias assessment	VPT AAT	✓	✓	✓	✓
Generalisation of training effects	BIAT	✓		✓	
Executive function	Stroop task	✓		✓	
Baseline measures	Demographics Case history details RSES	✓			
Primary outcome measure	Clinical status (lapse/relapse)	✓		✓	✓
Secondary outcome measures	AUDIT^a^ CORE Alcohol/Drug use^a^ OCDS STAI-Y BDI-II	✓		✓	✓
Motivation to treatment	MAC2-A	✓		✓	
	Motivation to training		✓		

^a^At baseline, post-intervention and follow-up measurement sessions, the questionnaire refers to the last 12, 1, and 3 months, respectively.

VPT: Visual Probe Task; AAT: Approach-Avoidance Task, BIAT: Brief Implicit Association Task, RSES: Rosenberg Self-esteem Scale, AUDIT: Alcohol Use Disorder Identification Test, OCDS: Obsessive-Compulsive Drinking Scale, STAI-Y: State-Trait Anxiety Inventory – Form Y, BDI-II: Beck Depression Inventory-II, MAC2-A: Motivation to Change-Alcohol version.

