### Data analysis

Complete analyses will be conducted in agreement with Intention-To-Treat principle [26]. Missing data points will be handled with multiple imputation.

To answer to the main research question, a multiple logistic regression will be used to estimate how much the main and combined exposure to the two CBM modules affects the occurrence of lapse and/or relapse episodes at the three-month follow-up assessment.

The secondary research question, whether participants approach and attentional biases do change after the CBM intervention, is addressed via a 3×2×3 repeated-measures mixed ANOVA with the AAT and VPT scores as dependent variables, time (baseline, post-intervention and follow-up) as repeated measures within-subject factor, drink type (alcoholic and non-alcoholic) or attentional process (engagement and disengagement) as within-subject factor, and CBM condition (re-training or placebo) as between-subject factor. The same analysis applies to the continuous secondary outcome measures administered at each time point.

The third research question of the present study is framed within a ‘what works best for whom?’ approach [8] and explores the moderating and mediating roles of individual differences variables on the clinical outcome by means of a moderated mediation analysis [51]. More precisely, baseline strength of the cognitive biases and interference control capacity (Stroop task), as well as age, gender and previous detoxifications, are hypothesised to moderate the change in cognitive bias after the CBM intervention, which is further hypothesised to eventually mediate the change in the clinical outcome variable (see Eberl *et al*. [19]).

Finally, participants’ motivation to change (MAC2-A) at pre- and post-intervention will be compared via a paired t-test. Via a repeated-measures ANOVAs we will explore whether change in participants’ motivation to carry on with the training after the brief MS interviews affects attrition and training outcome.

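### The exploratory mediation analysis measures bias change up to 45-50 days into training and does not use the lapse status recorded at that visit, so early drinking could pass for mediation

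*Protocol article*

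**What the plan says.** The abstract of the protocol article lists, within an exploratory analysis, "mediators (change in cognitive bias) of the primary outcome measure". Its aims section says of the expected bias changes that "these changes might mediate the effects on the clinical outcome". The Data analysis section plans a moderated mediation. The moderators it names are "baseline strength of the cognitive biases and interference control capacity (Stroop task), as well as age, gender and previous detoxifications". They act on the change in bias after training, "which is further hypothesised to eventually mediate the change in the clinical outcome variable".

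On timing, the Trial design section allows at most five days between training sessions and states: "The post-intervention assessment takes place between the 10th and 11th training session". Participants and procedure requires at least two months of abstinence at entry. The Outcome measures section defines the main outcome as lapse or relapse, yes or no, in the three months after the intervention. Table 1 has a clinical-status row (lapse/relapse) ticked at baseline, post-intervention and follow-up. Nothing in the Data analysis section assigns the post-intervention entry to the mediation model.

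**The concern.** A mediation claim needs two links: training changes bias, and bias change affects relapse. Randomisation protects the first but not the second. Participants are abstinent at entry, so any lapse during training is a new event after randomisation. The Background stresses that outpatients live in their usual environment and must abstain by their own effort, so such lapses are plausible. The same section describes "strengthened automatic reactions to substance-related cues that have acquired a high incentive salience after repeated consumption", which gives a route from drinking to higher bias.

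A lapse before the post-intervention visit could therefore raise measured bias and also mark a participant who will relapse later. Bias change and relapse would then be associated even if bias had no effect on relapse. Adjusting for baseline bias does not remove this, because the lapse comes after baseline. At stake is the reading of the mechanism: the Discussion presents understanding of how the training works as one of the trial's contributions.

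**Working it through.** The plan gives no figure for the mediation analysis, so there is none to reproduce. The timing can be computed; the size can only be simulated.

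**Time at risk before the mediator is measured** (Trial design: interval at most 5 days, assessment between sessions 10 and 11)
- Session 1 to session 10: 9 × 5 = 45 days at most.
- Session 1 to session 11: 10 × 5 = 50 days at most.
- The post-intervention measure therefore falls up to 45-50 days after session 1, plus an unstated gap from baseline.

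**How many might lapse by then.** The documents do not say. The Sample size section cites placebo relapse of 0.18 (a three-month study) and 0.60 (one-year studies). Assuming a constant hazard:
- 1 − (1 − 0.18)^(50/90) = 0.10
- 1 − (1 − 0.60)^(50/365) = 0.12

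Brief lapses may be commoner than relapses, so 10-30% was examined.

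**Simulation with no true effect of bias on relapse.** One module, 60 v 60, 2,000 trials per row.
- Baseline bias ~ N(0, 1).
- Post bias = 0.6 × baseline − 0.5 × training + rise × lapse + N(0, 0.8²).
- Lapse is independent of training and bias.
- logit P(relapse) = constant + ln(OR) × lapse, with overall relapse set to 60%.
- Equation 1 (least squares): bias change on training and baseline bias.
- Equation 2 (logistic): relapse on bias change, baseline bias and training.
- False mediation: the training term in equation 1 and the bias-change term in equation 2 both significant at two-sided 5%.

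Assumed inputs, since the documents give none: lapse 10-30%, rise 0-1 SD, lapse-relapse OR 4 or 8.

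| Lapse by post-intervention | Rise in bias | False mediation, OR 4 | False mediation, OR 8 |
|---|---|---|---|
| 10% | 0.3 SD | 4% | 4% |
| 10% | 0.5 SD | 5% | 6% |
| 10% | 1.0 SD | 8% | 12% |
| 20% | 0.3 SD | 5% | 6% |
| 20% | 0.5 SD | 7% | 11% |
| 20% | 1.0 SD | 16% | 25% |
| 30% | 0.3 SD | 7% | 10% |
| 30% | 0.5 SD | 11% | 19% |
| 30% | 1.0 SD | 27% | 44% |

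With no rise in bias the rate is 4-5%. Adding lapse status to equation 2, or dropping those who lapsed, brings it to 4-5% in every row.

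**Cross-check with other inputs** (lapse-relapse OR 3 or 6, training effect 0.5 or 0.8 SD): false mediation is about 4-6% for a rise of 0.3 SD or less. With 30% lapsing and OR 6, it is 11-16% for a 0.6 SD rise and 22-32% for a 1 SD rise. At n = 20,000 the false indirect effect stays at −0.07 to −0.14 log-odds, so it is bias and not chance.

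**Cost of adjusting when mediation is real.** The same model was run with a direct effect of 0.4 log-odds of relapse per SD of bias, 0.8 log-odds of lapse per SD of bias, about 20% lapsing, lapse-relapse OR 6 and no rise from lapse. Detection by joint significance falls from 56% to 32% after adjustment, and to 25% in the no-lapse subset.

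**The case against.** The strongest reply is that this is an unstated detail and not an error. The variables named in the Data analysis section moderate the training-to-bias path. The article fixes no covariate set for the relapse equation, and an analysis plan that is not shown could add one. That is right as far as it goes: a reader might infer that the plan has deliberately excluded early lapses, and the text does not support that. What stands is narrower. The analysis as described contains nothing that establishes that bias change came before drinking, although the needed record is collected. The references to change in the clinical outcome could hint at using earlier status, but the Outcome measures section defines a yes/no outcome after the intervention.

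Second, the Background speaks of repeated consumption, which is a history of use and not a single lapse. That stands too. The documents support the direction of the effect but no size, and with a small rise in bias the error rate is close to nominal.

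Third, the analysis is exploratory and the wording is cautious. This limits the consequence but does not remove it.

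Fourth, if lower bias prevents lapses, an early lapse lies on the causal path and adjusting for it hides real mediation. This stands, and it decides the form of the fix.

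**Conclusion.** The concern holds as a limit on what the exploratory mediation analysis can show. Taking the mediator as baseline-to-post-intervention change (the natural reading, though the time point is not stated outright), it is measured up to 45-50 days after session 1, and lapses before that visit can create or inflate the bias-to-relapse link.

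The size is unknown. Under the assumptions shown, false mediation is near nominal to about 12% if 10-20% lapse and bias rises by 0.3-0.5 SD. It reaches 25% or more only with 20-30% lapsing, a rise of about 1 SD and a strong lapse-relapse link.

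Three stronger readings are tempting and unsupported:
- That a mediation finding from this trial would probably be spurious. The documents give no lapse rate during training and no effect of a lapse on bias.
- That error rates above 50% apply to the mediation claim. Such figures arise for the single bias-to-relapse coefficient in the most extreme scenarios; the mediation claim also requires the training-to-bias link.
- That the primary result is compromised. The primary logistic regression compares randomised groups and does not involve bias change.

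**What to change.** Keep the planned moderated mediation and state that its mediator is the change from baseline to post-intervention. Report two sensitivity analyses beside it:

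- (a) the relapse equation with clinical status (lapse/relapse) at post-intervention added;
- (b) the analysis restricted to participants with no lapse by post-intervention.

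If the bias-to-relapse path disappears in these, report that reverse causation from early drinking cannot be excluded, and do not present bias change as the established mechanism.

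The cost is a few sentences in the analysis plan and no new data, since Table 1 already schedules the variable. The downside is real: lapse during training may itself be affected by training or by bias, so both analyses can remove part of a true indirect effect and lose power, and (b) also selects on an event after randomisation. They should be read as sensitivity analyses and not as a gate for claiming mediation.
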